#### Sample size {14}

This is a randomized controlled trial. The bilateral significance level is 5% with an assurance of 90%. We estimate the standard deviation is 36 h, and the mean difference is 36 h. In the case of 1:1 ratio between intervention group and control group, a total of 44 patients will be needed (22 patients in each group). Considering a 20% drop-out rate, 56 patients will be recruited.

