### Statistical methods

#### Statistical methods for primary and secondary outcomes {20a}

Intention-to-treat (ITT): Nno one was excluded from the main analysis set after randomizationPer-protocol set (PPS): good compliance case data that meets the main inclusion and exclusion criteria and reach the primary endpoint

The number of participants selected and complete the study will be listed and the two analysis data sets (ITT and PPS) as specified above will be identified. Cases of protocol violation will also be listed with reasons documented. In terms of outcome indicator analysis, continuous variable indicators will count the number of cases (*n*), mean (*x*), standard deviation (SMD), median (*M*), minimum (min), and maximum (max). The difference between groups will be analyzed using Student’s *t*-test. Counting and grading data will be used to calculate the frequency and composition ratio. The *χ*
^2^ test/chi-square test will be used for differences between groups. Unless otherwise stated, all statistical tests will be conducted in a bilateral manner. All data will be entered in Microsoft Excel, and all statistical analyses will be performed using the SPSS version 25 statistical package.

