#### Adverse event reporting and harms {22}

All participants will be monitored with respect to any possible adverse events related to the administration of interventions. All adverse events (AEs) observed or reported by the participants or clinical doctors are collected and evaluated for relatedness to trial intervention, seriousness, severity, expectedness, and outcome by study team. All adverse events will be documented and reported to IRB.

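### Graded data are sent to the chi-square test, which ignores the order of the grades; a minor point that applies only if an outcome has three or more ordered grades

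*Protocol article*

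**What the plan says.** Statistical methods for primary and secondary outcomes {20a} divides outcomes into two classes. Continuous variables are compared by Student's t-test. For the rest, "Counting and grading data will be used to calculate the frequency and composition ratio", and then the "chi-square test will be used for differences between groups". Ordered categories are therefore named as a data type and share a test with unordered ones. No rank, trend or ordinal method appears elsewhere in the article, and Methods for additional analyses {20b} plans no subgroup or adjusted analysis.

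Outcomes {12} does not define any outcome as graded:

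- Mortality, new-onset organ failure and abdominal infection are yes/no, and the safety outcome is a proportion of adverse and serious adverse events.
- The primary outcome, timing of enteral nutrition, intra-abdominal pressure, lengths of stay and cost are times or continuous measures.
- Borborygmus is assessed daily, with no scale given here or in Plans for assessment and collection of outcomes {18a}.

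Adverse event reporting and harms {22} says that events are "evaluated for relatedness to trial intervention, seriousness, severity, expectedness, and outcome by study team". That describes how events are assessed. It is not a planned between-arm test of severity grade.

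**The concern.** With three or more grades, Pearson's chi-square treats the grades as labels. Permuting the columns of the 2 × k table leaves the statistic and the p-value unchanged. The test spends k − 1 degrees of freedom on any difference in pattern, whereas the trial's question is directional: Objectives {7} asks whether neostigmine promotes recovery of intestinal function. A consistent movement towards better grades can therefore be missed. A difference with no direction, such as more patients at both extremes, can come out significant.

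If borborygmus is graded, a secondary measure of motility would be compared by a test with less power than the same data allow, in a trial with at most 28 patients per arm. The article has already chosen the test for graded data, so the choice is not simply left open for a later analysis plan. A plan that follows the article inherits the weakness, and one that departs from it contradicts the published text.

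**Working it through.** **Inputs from the document** (Sample size {14}): "The bilateral significance level is 5% with an assurance of 90" percent; "We estimate the standard deviation is 36 h, and the mean difference is 36 h"; "a total of 44 patients will be needed (22 patients in each group"); "Considering a 20% drop-out rate, 56 patients will be recruited".

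**The plan's own figure.** Normal approximation: n per arm = 2 × (1.960 + 1.282)² × (36/36)² = 2 × 3.2415² = 21.01, rounded up to 22. The t-based solution is 22.02 per arm, with power 0.8997 at 22. Drop-out: 22 / 0.8 = 27.5, rounded up to 28 per arm, 56 in total. The stated figures reproduce. They concern the primary outcome only; the article claims no power for a graded outcome.

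**Inputs the document does not give (assumptions).** Number of grades: 3, 4 or 5. Spread over grades in the control arm: equal, or several sets of unequal shares. Effect: a one-way shift, expressed either as a common odds ratio of 2 to 8 or as a shift of 0.5 to 1.0 SD on an underlying normal scale.

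**Method.** 20,000 simulated trials per scenario at 22 and 28 per arm. Pearson's chi-square (k − 1 df) was compared with the tie-corrected Wilcoxon rank-sum test at two-sided 0.05. With no effect, chi-square rejected in 3.9% to 5.3% of trials and Wilcoxon in 4.6% to 5.3%.

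**Power, chi-square / Wilcoxon, equal shares in the control arm:**

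| Per arm | Grades | OR 2 | OR 4 | OR 8 |
|---|---|---|---|---|
| 22 | 3 | 17.9% / 22.6% | 55.9% / 65.8% | 86.4% / 92.0% |
| 22 | 4 | 15.6% / 23.9% | 50.5% / 68.6% | 84.2% / 94.3% |
| 22 | 5 | 13.2% / 24.0% | 46.4% / 70.3% | 82.1% / 95.2% |
| 28 | 3 | 21.9% / 28.1% | 66.4% / 76.4% | 93.8% / 96.9% |
| 28 | 4 | 19.2% / 29.4% | 62.4% / 79.3% | 93.3% / 98.1% |
| 28 | 5 | 17.2% / 30.5% | 58.2% / 80.3% | 92.1% / 98.5% |

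**Range over all odds-ratio scenarios, unequal shares included.**

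- Smallest gain for Wilcoxon: 96.9 − 93.8 = 3.1 points (28 per arm, 3 equal grades, OR 8).
- Largest gain: 63.0 − 36.5 = 26.5 points (22 per arm, 5 unequal grades, OR 4).

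**Underlying normal shift of 0.5 to 1.0 SD, equal grades.** The gain runs from 6.1 points (22 per arm, 3 grades, 0.5 SD) to 24.4 points (22 per arm, 5 grades, 0.8 SD).

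**Where the advantage disappears.**

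- Two categories, 28 per arm, OR 3: chi-square 50%, Wilcoxon 47%. Wilcoxon gains nothing.
- A non-monotone difference, in one assumed pattern: chi-square 89%, Wilcoxon 6%. The ranking reverses.

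**The case against.** The strongest objection is about reach. No listed outcome is defined as graded. If borborygmus is recorded as a rate, {20a} sends it to the t-test; if as present or absent, chi-square is suitable. A condensed article may also leave the scale to the full protocol, so its absence is not a fault in itself. All of this stands, and it makes the point conditional. It does not remove it, because the article names graded data as a class and fixes the test for it.

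Three stronger readings are tempting, and the document does not support them.

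- *The plan loses a known amount of power.* None of the inputs for that figure (number of grades, their distribution, the effect) is in the article. The standardised effect of 1 comes from hours to first defecation and cannot simply be carried over to bowel sounds. The range holds only under the stated assumptions.
- *The comparison of adverse-event severity is weakened.* No such comparison is planned. Severity is assessed for each event, and the listed outcome is a proportion.
- *The analysis cannot show a direction.* That is true of the test statistic alone. The planned frequencies and composition ratios show direction descriptively, and with yes/no outcomes it is read from the two proportions.

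**Conclusion.** The point holds in a limited, conditional form and is minor. The rule in {20a} is a poor choice for any outcome with three or more ordered grades, because it discards the order and answers a question about pattern when the trial asks about direction. The loss against Wilcoxon is roughly 3 to 27 percentage points of power, assuming 3 to 5 grades, 22 to 28 patients per arm and a one-way shift. It tends to grow with the number of grades. Borborygmus is the only listed candidate, and only if it is graded. The primary outcome, the sample size and the yes/no secondary outcomes are unaffected.

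**What to change.** In {20a}, separate the two data types. Keep the chi-square test for binary and unordered outcomes. For graded outcomes use the Wilcoxon rank-sum test, or a proportional-odds model reporting a common odds ratio with its 95% confidence interval, on one pre-specified value per patient. If borborygmus is graded, name its scale and the day or summary that turns the daily readings into that single value; without this the analysis is not determined. Continue to tabulate frequencies and proportions by grade. If no outcome is graded, delete the reference to graded data.

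The cost is a sentence or two. No new data or patients are needed, and the rank-sum test is available in SPSS 25, the package the article names. The one downside is lower sensitivity to a non-monotone difference, which is not what the trial asks. The change is best made before any unblinded analysis: Who will be blinded {17a} leaves the data analysts unblinded, so a later switch of test could look driven by the data.

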#### Interim analyses {21b}

No planned interim analyses will be arranged because of relatively small sample size of this study.

#### Methods for additional analyses {20b}

Currently, there is no planned additional subgroup or adjusted analyses.

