### Eligibility criteria {10}

The detailed inclusion and exclusion criteria are outlined in Table 1. Briefly, patients with newly onset of acute alcoholic or hyperlipidemia AP and evidence of organ failure will be included. Patients that have contraindication to neostigmine methylsulfate injection or other severe diseases will be excluded.

**Table 1 Tab1:** Eligibility criteria

Inclusion criteria	Exclusion criteria
• Aging between 18 and 75 • Diagnosed with alcoholic or hyperlipidemia acute pancreatitis • Evidence of organ failure (according to Marshall scoring system)	• Allergic to neostigmine methylsulfate injection • Contradiction to neostigmine methylsulfate injection ▪ Epilepsy ▪ Angina, arrhythmia, ventricular tachycardia, sinus bradycardia, ▪ Mechanical intestinal obstruction, urethra tract obstruction, asthma ▪ Uncontrolled hypotension, elevated vagus nerve tone • Pregnancy • Uncontrolled hypertension and severe cardiocerebrovascular disease

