### Assignment of interventions: allocation

#### Sequence generation {16a}

All participants will be randomly divided into the intervention group or the control group in a 1:1 ratio. Randomization will be performed using computer-generated sequence. No stratification is planned in this study.

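### The primary comparison is left unadjusted in a small, unstratified trial; pre-specifying baseline Marshall score as a covariate would be a cheap, modest gain in precision

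*Protocol article*

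**What the plan says.** - Methods for additional analyses {20b}: "Currently, there is no planned additional subgroup or adjusted analyses".
- Sequence generation {16a}: allocation is 1:1 by computer-generated sequence, and "No stratification is planned in this study".
- Statistical methods {20a}, on continuous outcomes: "The difference between groups will be analyzed using" Student's t-test. The primary outcome, time from disease onset to first spontaneous defecation, falls under this rule.
- Sample size {14}: "The bilateral significance level is 5% with an assurance of 90" per cent; "We estimate the standard deviation is 36 h, and the mean difference is 36 h"; "a total of 44 patients will be needed (22 patients in each group"), raised to 56 for 20% drop-out.
- Eligibility criteria {10}, Table 1: "Evidence of organ failure (according to Marshall scoring system") is an entry condition for every patient.
- Outcomes {12}: new-onset organ failure counts only failure that was absent at all times before randomisation, so baseline organ status has to be known for each patient.
- Who will be blinded {17a}: the data analysts are not blinded.

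**The concern.** With 22 to 28 patients per arm and no stratification, the arms can differ noticeably in baseline severity by chance. The protocol itself ties severe dysmotility to the gravest forms of the disease (Background and rationale {6a}), so severity is a reasonable candidate for a prognostic factor, though no passage quantifies its link with time to defecation. If severity does matter, an unadjusted comparison leaves its contribution in the error term, which widens the confidence interval. Any severity imbalance that appears also goes unaddressed in the planned analysis.

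There is a procedural side as well. The word that opens the quoted sentence in {20b} leaves later adjustment open, and the analysts know the allocation. If a covariate is added only after an imbalance is noticed, it is chosen by people who can see which arm it favours. Naming it in advance closes that route.

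**Working it through.** **Inputs.** From Sample size {14}: two-sided alpha 5%, power 90%, SD 36 h, difference 36 h, 22 per arm, 20% drop-out. Not in the protocol, hence assumed: R², the share of outcome variance explained by baseline Marshall score, taken from 0 to 0.30.

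**Step 1: reproduce the plan's figure.** n per arm = 2(1.960 + 1.282)² × (36/36)² = 21.01, rounded up to 22, so 44 in total. Drop-out: 22/0.8 = 27.5, rounded up to 28, so 56. Exact noncentral-t power at 22 per arm with 42 degrees of freedom is 89.97%. The plan's figures hold.

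**Step 2: unadjusted precision.** SE = 36 × √(2/22) = 10.85 h. The 95% half-width is 2.018 × 10.85 = 21.9 h.

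**Step 3: adjust for one covariate.** The residual SD is 36 × √(1 − R²). Estimating one covariate effect when the arms differ by chance costs an average variance factor of 1 + 1/(N − 4) = 1 + 1/40 = 1.025, and one degree of freedom (42 to 41). So SE = 36 × √(1 − R²) × √1.025 × √(2/22), and the half-width is 2.020 × SE.

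| R² (assumed) | SE, h | 95% half-width, h | Power at 36 h |
|---|---|---|---|
| Unadjusted | 10.85 | 21.9 | 90.0% |
| 0 | 10.99 | 22.2 | 89.2% |
| 0.10 | 10.43 | 21.1 | 92.1% |
| 0.20 | 9.83 | 19.9 | 94.7% |
| 0.30 | 9.19 | 18.6 | 96.9% |

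Break-even: the SEs are equal when (1 − R²) × 1.025 = 1, that is R² = 0.024. Allowing for the lost degree of freedom, it is about 0.025.

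**Step 4: is the unadjusted test valid?** In simulation (10,000 runs per setting, 22 per arm, covariates explaining 0 to 50% of variance and ignored by the t-test), its type I error ran from 4.7% to 5.3%. Chance imbalance is already allowed for in its standard error.

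**Step 5: how large can imbalance be?** For a baseline factor present in half the patients (an assumed prevalence), the arms differ by 20 points or more with probability 17% at 22 per arm and 14% at 28 per arm. If that factor explained 10% of variance, its effect would be 36 × √0.10 / 0.5 = 22.8 h, and a 20-point imbalance would shift the estimate by 0.2 × 22.8 = 4.6 h. That is less than half the 10.85 h standard error.

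**The case against.** The strongest reply is that nothing here is wrong. The unadjusted t-test is unbiased over randomisation and keeps its error rate, the trial is sized for exactly that test using the total SD, and an unstratified design with an unadjusted analysis is coherent. All of this stands. A reader might infer that the missing stratification makes the comparison invalid, or that the trial is underpowered against its own target. Steps 1 and 4 support neither.

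The prognostic value of severity is also undocumented. Every patient must have organ failure to enter, which narrows the range of the score and may weaken its effect. This stands too, and it is why R² = 0 is in the table. The cost in that case is 0.8 points of power at the planned difference.

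The protocol does not say that a numeric Marshall score is kept; Table 1 uses the system only as a threshold. So the score is best described as assessed at entry, not as already recorded, and the fix has to ask for it to be recorded.

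It may be tempting to add aetiology, since alcoholic or hyperlipidaemic cause is also an entry criterion. Being available does not make it prognostic, and nothing in the protocol links it to time to defecation. With two covariates the power at R² = 0 falls to 88.4% and break-even rises to about R² = 0.05.

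Finally, covariates are often settled in the statistical analysis plan, which is not shown. The point rests on what {20b} states positively, not on silence.

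**Conclusion.** The point holds as an inexpensive improvement, not as an error or contradiction. The protocol plans no adjusted analysis in a small unstratified trial, although severity is assessed in every patient before entry.

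On the protocol's own 36 h difference and SD, one severity covariate is worth about 2 to 7 points of power and about 1 to 3 h of confidence interval half-width if it explains 10% to 30% of the variance. It costs under 1 point of power and 0.3 h of half-width if it explains none. These sizes rest on the assumed R², on 22 analysed per arm and on a linear model with normal errors.

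It would overstate the text to say that adjustment is ruled out: {20b} says only that none is planned at present. It would equally overstate the case to say that precision is certainly lost, since that depends on R² exceeding about 0.025.

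**What to change.** Replace the sentence in Methods for additional analyses {20b} with wording such as: *The primary comparison will be adjusted by analysis of covariance for total Marshall score at randomisation, recorded at the eligibility assessment. The unadjusted Student's t-test will be reported alongside. No subgroup analyses are planned.*

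Align Statistical methods {20a} with this, and add the total score to the baseline data to be collected. Date the change before any outcome data are seen, because the analysts are unblinded. Leave aetiology out of the model.

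The cost is one sentence, one recorded number per patient from an assessment already required for entry, one degree of freedom, and the small loss of power given above if severity proves not to be prognostic. No extra patients or procedures are needed.

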#### Methods in analysis to handle protocol non-adherence and any statistical methods to handle missing data {20c}

An ITT data set will be used for protocol non-adherence and no imputation of missing data will be performed for statistical analysis.

#### Plans to give access to the full protocol, participant level-data and statistical code {31c}

Any data required to support the protocol can be supplied on reasonable request. Only de-identified datasets will be supplied.

### Oversight and monitoring

#### Composition of the coordinating center and trial steering committee {5d}

This is a single-center trial. The study team will coordinate and manage the entire study process. A regular meeting will be arranged to discuss study questions of any type. An IRB consisting of three experts not involved in this study will be formed to monitor the trial.

#### Composition of the data monitoring committee, its role and reporting structure {21a}

This is a single-center trial with relatively small sample-size, data monitoring will therefore be conducted by study team. No data monitoring committee is required.

#### Adverse event reporting and harms {22}

All participants will be monitored with respect to any possible adverse events related to the administration of interventions. All adverse events (AEs) observed or reported by the participants or clinical doctors are collected and evaluated for relatedness to trial intervention, seriousness, severity, expectedness, and outcome by study team. All adverse events will be documented and reported to IRB.

#### Frequency and plans for auditing trial conduct {23}

For the quality assurance, 20% randomly selected data from the collected information will be re-interviewed. Any discrepancies will be corrected accordingly. In addition, the IRB will audit the data every month.

#### Plans for communicating important protocol amendments to relevant parties {25}

The principal investigator will be responsible for any protocol modification and any modification will be submitted to the Research Ethics committee of PUMCH for approval. The principal investigator will disseminate the changes of the protocol and all team members will be trained.

#### Dissemination plans {31a}

The study findings will be presented in national or international conferences. A full scientific article will be developed and published in peer-reviewed journal/s. The results of the study will be released to the participating patients.

## Discussion

Gastrointestinal dysmotility is a common complication in AP patients, which can lead to delayed feeding and OFI. There is little evidence regarding the treatment of gastrointestinal dysmotility induced by AP. Neostigmine can increase gastrointestinal motility and has been used to treat gastrointestinal dysmotility after surgery. With this randomized, placebo-controlled trial, our aim is to investigate whether neostigmine is safe and efficacy for treating AP patients with gastrointestinal dysmotility. We would like to discuss some aspects and challenges of the study design in detail below.

First, the enrollment of patients: a diagnosis of SAP requires persist organ failure, which is defined as organ failure lasting over 48 h [4]. However, early intervention [38] plays an important role in treating AP patients, so we start intervention on patients within 24 h of onset, which will lead to brief intervention on moderate-severe acute pancreatitis patients.

Another point we would to address is the COVID-19 pandemic, which may lead to fewer patients, disturbing patient enrollment and even temporary interruption of the research. A delayed end of this study may occur.

In conclusion, a positive outcome of this trial will provide strong evidence as to the safety and efficacy of neostigmine in treating the gastrointestinal dysmotility for AP patients.

### Trial status

The study is on its third version of the protocol and is expected to begin enrollment on May 1, 2022. Completion of the study protocol is expected to be near May 1, 2024, and the estimated end of study date will be September 1, 2024.

## Data Availability

All data are stored securely with the corresponding author on an organizational password-protected computer/network and will be destroyed 5 years after the study’s conclusion. The datasets analyzed during the study will be made available from the corresponding author on reasonable request. If the subjects are infringed due to data disclosure in the trial, the research team will provide them with appropriate compensation if necessary.

## Abbreviations

IRB: Institutional review board
AP: Acute pancreatitis
SAP: Severe acute pancreatitis
OFI: Oral feeding intolerance
ACS: Abdominal compartment syndrome
ACI: Acetylcholinesterase inhibitor
IAP: Intra-abdominal pressure
ICU: Intensive care unit
PUMCH: Peking Union Medical College Hospital
ICF: Informed consent form
ITT: Intention-to-treat
PPS: Per-protocol set
AE: Adverse event
